**Figure 1 fig1:**
[figure not shown]
Overview of the clinical (top) and parallel study-related (down) workflows. TCSC, Thrombectomy Capable Stroke Center; PSC, Primary Stroke Center.

The collection tubes are pre-packed and labeled with unique alphanumeric codes generated by the Charité independent data trust office. These codes include the prefix “LVO- “and a 9-digit random number.

For blood collection, 3 EDTA- tube (4 mL, purple lid) and one Heparin-tube (4 mL, green lid; BD Vacutainer®, Becton, Dickinson and Company, Franklin Lakes, New Jersey, United States) are utilized. Following collection, the tubes are inverted 8–10 times to mix the blood with the preservant and processed at room temperature within 30 min.

The samples are then centrifuged at 2,000 g for 15 min (CompactStar CS4, by avantor™, delivered by vwr™, Radnor, PA, USA, and CD-0506, Phoenix Instrument, Garbsen, Germany). Additionally, a second POCT will be conducted using 15 μL of heparin plasma obtained post-centrifugation, and results will be documented as described above. Finally, the remaining volume of plasma samples is pipetted and divided into 250 μL aliquots in cryotubes, maintaining the color code for each sample type (e.g., Plasma EDTA in purple-lid cryotubes and Heparin in green-lid cryotubes). These cryotubes are placed in a storage box with individual compartments for each sample.

The storage box is placed in a styrofoam container and kept in the MSU refrigerator at 4 °C before being transferred to a − 20 °C freezer at the MSU site within 30 min to 4 h. Within four weeks, samples are transported to the biobank at Charité—Campus Benjamin Franklin, where they are stored at −80 °C. Sample and box positions are recorded throughout the process (Supplementary Figure 1). Patients will have the option to donate the remaining volume of blood samples for additional research purposes, such as the evaluation of other biomarkers. Residual plasma samples will be processed and stored as described above.

Study-related use of analysis results and/or additional blood samples will begin only after written informed consent is obtained from the patient or their legal representative. If written consent is not provided within 12 weeks of sample collection, the patient is classified as a dropout, and all associated samples and data are destroyed.

### Description of the LVOCheck POCT device

In the initial clinical study subproject, LVOCheck-Opti (DRKS00030399), plasma samples were collected that allowed the technical performance (analytical accuracy) of the LFA. LVOCheck is a device under development by the project partner Advanced Brain Companion Diagnostics, S. L. (ABCDx, [name]). This test is currently under development and not available for clinical use.

This portable, non-invasive and rapid solution is designed to predict LVO risk in pre-hospital emergency settings by integrating a blood-based multi-biomarker single LFA– measuring NT-proBNP, D-Dimer and H-FABP– with patient-specific clinical parameters all accessible and guided through a Mobile App.

The single LFA within the assay consists of a sample application pad, a conjugate pad preloaded with analyte-specific antibodies conjugated to a detection label, and a nitrocellulose membrane containing immobilized capture antibodies specific to either NT-proBNP, D-Dimer or H-FABP. Upon blood sample application, a buffer solution must be added to facilitate sample migration through the control and three biomarker test lines on the LFA strip.

After the incubation period of 10 min, results can be easily scan using the App, just positioning the smartphone above the POCT. The scan measures the intensity of the control and test lines to generate numerical signals based on colorimetry for each biomarker, which are ultimately converted into biomarker concentrations using lot-specific calibration curves.

The LFA is designed for use with a digital reader that quantifies the intensity of the test line signals and integrates clinical parameters for enhanced diagnostic accuracy. Respective thresholds have been determined with samples and clinical data from the first subproject, LVOCheck-Opti, as well as the BIO-FAST study (NCT04612218).

Additionally, patient-specific clinical data is registered by the HCP through the App, including patient ID number, age, blood pressure and neurological scale assessment [to choose between: NIHSS (National Institutes of Health Stroke Scale), Cincinnati (Cincinnati Prehospital Stroke Severity Scale), RACECAT (Rapid Arterial Occlusion Evaluation for CATalonia), G-FAST (Cincinnati Stroke Scale-Modified for Gaze, Face, Arm, Speech, and Tim)]. No data allowing for patient identification is entered into the Mobile App. For study purposes, full NIHSS assessment will be performed through the Mobile App.

Finally, after integrating the biomarker concentrations and patient-specific clinical parameters, the predictive LVO risk is calculated by the software component. The Mobile App temporarily displays output data (biomarker concentrations and LVO stroke risk/probability) alongside the clinical input data (age, blood pressure, stroke assessment score), while simultaneously being transmitted to the WebPortal communication system for secure and long-term storage. Additional clinical information, comprising patient final diagnosis, is documented by the treating physician in the eCRF. Due to the MSU’s specialized staffing structure, brief sample handling, and automated smartphone-based notifications, the proposed POC test integrates seamlessly into routine clinical workflows, allowing patient care to proceed without interruption and without prolonging on-scene time.

### Data storage and management

All clinical data collected and biosamples from participants are pseudonymized by assigning a unique identification number, generated by the Charité data trust office (CHA-THS). Each study site maintains a secure pseudonymization list linking identification numbers to participants’ full names and dates of birth for potential identification if necessary. This list remains confidential, is stored exclusively at the study site, and will be archived for at least 10 years post-study completion. Pseudonymized data is entered into an eCRF and managed using REDCap, hosted by Charité—Universitätsmedizin Berlin. Additionally, study participation is documented in the patient’s medical record.

The Mobile App securely manages patient session data for up to 24 h. During this period, users can access patient information—including input data, vascular biomarker concentrations (NT-proBNP, D-Dimer and H-FABP), and calculated LVO stroke probability—by entering their personal PIN code. After 24 h, all data is automatically deleted from the Mobile App.

For long-term storage, patient sessions are transferred to a secure cloud infrastructure and can be viewed through the LVOCheck communication system Access to this portal is restricted to ABCDx administrators only. All entries are organized and sortable by project ID and participant code.

## Definitions

This study will adhere to the definitions previously outlined in the LVOCheck-Opti subproject.

### Ischemic stroke

An episode of neurological dysfunction caused by focal cerebral, spinal, or retinal infarction, while infarction is brain, spinal cord, or retinal cell death attributable to ischemia, based on pathological imaging or clinical evidence of cerebral, spinal cord, or retinal focal ischemic injury based on symptoms persisting ≥24 h or until death, and other etiologies excluded.

### Large-vessel occlusion

Occlusion of blood vessels supplying the brain, detectable by angiography, generally comprising the Internal Carotid Artery (ICA), Middle Cerebral arteries segments 1 and 2 (M1 and M2) and Basilar Artery (BA).

### Intracerebral hemorrhage

Rapidly developing clinical signs of neurological dysfunction attributable to a focal collection of blood within the brain parenchyma or ventricular system that is not caused by trauma.

### Stroke mimic

Certain diseases like syncope, epileptic seizure, hypoglycemia, hyperglycemia, migraine aura, dissociative disorder etc. that can cause similar symptoms as stroke. A stroke is initially clinically suspected, but the diagnostic criteria of stroke are not fulfilled.

## Statistics

### Sample size estimations

The sample size was determined based on the precision achievable for sensitivity and specificity estimates, as measured by confidence interval (CI) widths. We estimate that 14.4% of stroke-alert patients will have an LVO diagnosis, based on prior data (internal STEMO data) derived from a preliminary study where 260 of 1,800 patients were diagnosed with LVO. We anticipate achieving a sensitivity of at least 75% and a specificity of at least 95%. For a cohort of 800 patients, the 95% CI for sensitivity would span ±8.26 percentage points (75% ± 8.26%), while the 95% CI for specificity would span ±1.7 percentage points (95% ± 1.7%). These levels of precision are considered sufficient for determining the diagnostic accuracy of the LVOCheck multiplex tool in this new cohort.

## Statistical analysis

A detailed statistical analysis plan will be provided before the analyses of the data. Descriptive statistics, including mean, standard deviation, median, and interquartile range (IQR), will be reported for key variables such as patient age. Predictions for each patient will be generated using the regression model developed in the previous phase and compared against the confirmed diagnoses to estimate sensitivity, specificity, accuracy, and corresponding 95% CIs. Exploratory subgroup analyses will be conducted to explore potential differences across demographic or clinical strata.

### Statistical analysis of the primary hypothesis

The definitive diagnosis of LVO as documented in the physician’s letter will serve as the reference standard for the analysis (Comparator). Multiple predictive models will be constructed to estimate each patient’s probability of LVO. Independent variables will include H-FABP, D-Dimer and NT-proBNP, and relevant clinical parameters readily available in the acute setting. The primary goal is to assess whether incorporating biomarker levels measured through POCT along with an LVO prediction diagnostic accuracy beyond what can be achieved with standard clinical information alone. Consequently, models that include both biomarkers and baseline clinical data will be compared against models featuring only clinical data. Key metrics such as sensitivity, specificity, positive predictive value (PPV) and negative predictive values (NPV) will be calculated to assess the diagnostic accuracy in detecting LVO in suspected stroke patients. Receiver Operating Characteristic (ROC) analysis will be used to evaluate overall diagnostic performance, with confidence intervals computed for all metrics to assess precision. Various predictive models will be examined iteratively which sensitivity is maximized while preserving a specificity level of at least 92.5%. This approach will characterize the real-world diagnostic accuracy of the POCT for LVO-prediction.

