## Hypotheses

### Primary study hypothesis

We hypothesize that combining POCT-based measurements of NT-proBNP, D-Dimer, and H-FABP with patient-specific clinical data, will enable pre-hospital identification of LVO in suspected stroke patients with a sensitivity of 50% and a specificity of 92.5%.

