### Primary endpoints

The primary endpoint of the study is the accuracy of LVOCheck, integrating patient-specific clinical data and POCT-based measurements of H-FABP, D-Dimer, and NT-proBNP, to predict LVO probability, evaluated against the gold-standard final hospital diagnosis, expressed as sensitivity and specificity.

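### Added value over clinical data is called the primary goal, but hypothesis, endpoint and sample size cover only the combined test, and model searching in this cohort conflicts with the model fixed earlier

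*Protocol article*

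**What the plan says.** All references are to the protocol article.

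**The goal.** The section Statistical analysis of the primary hypothesis states as its primary goal to learn whether biomarkers bring accuracy "beyond what can be achieved with standard clinical information alone". To that end, "models that include both biomarkers and baseline clinical data will be compared against models featuring only clinical data".

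**The hypothesis, endpoint and size.**
- The Primary study hypothesis is that the combination identifies LVO "with a sensitivity of 50% and a specificity of 92.5"%. It names no comparator.
- The Primary endpoints section takes the accuracy of LVOCheck, "evaluated against the gold-standard final hospital diagnosis, expressed as sensitivity and specificity". Again there is no comparator.
- Under Sample size estimations, "The sample size was determined based on the precision achievable for sensitivity and specificity estimates".

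**The models.** The same analysis section says that several models will be constructed, and examined iteratively so that sensitivity is as high as possible with specificity of at least 92.5%. It mentions no validation step. Two other sections point elsewhere. Statistical analysis says that each patient's prediction comes from the regression model of the previous phase. Description of the LVOCheck POCT device says that thresholds have already been determined from LVOCheck-Opti and BIO-FAST.

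**The concern.** The goal is comparative: what does blood add to the neurological score, age and blood pressure? The hypothesis, endpoint and sample size are not comparative. LVOCheck takes a full NIHSS, age and blood pressure as inputs, so nothing in the success criteria stops the clinical inputs from carrying the result. The primary endpoint could succeed while the assay contributes nothing, yet the Introduction and Discussion present the study as a test of whether the combination improves LVO detection.

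The second issue is which model is being judged. If models are built and selected in the same 800 patients in whom their sensitivity is reported, that sensitivity is too high. Any gain credited to the biomarkers can be too high as well, because the biomarker models have more predictors to search over.

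**Working it through.** **1. What the sample size was built for.** Inputs from Sample size estimations: "We estimate that 14.4% of stroke-alert patients will have an LVO diagnosis"; "We anticipate achieving a sensitivity of at least 75% and a specificity of at least 95"%; and "For a cohort of 800 patients, the 95% CI for sensitivity would span ±8.26 percentage points (75% ± 8.26"%), with ±1.7 points for specificity.

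- LVO patients: 800 × 0.144 = 115.2. Non-LVO patients: 800 − 115.2 = 684.8.
- Exact (Clopper–Pearson) 95% interval, half of total width, at 75% of 115.2: (82.60 − 66.07)/2 = 8.26 points.
- The same at 95% of 684.8: (96.51 − 93.09)/2 = 1.71 points.

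Both stated figures reproduce as one-sample intervals, so 800 was chosen for the accuracy of one test. No figure for a difference between two models enters.

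**2. What 115 LVO patients offer for the difference.** The documents give neither the clinical-only sensitivity nor the share of LVO patients whom the two rules classify differently (discordance, s). Both are assumptions here. For a gain d, McNemar test, two-sided 5%:

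power = Φ{ (d√n − 1.96√s) / √(s − d²) }, 95% half-width = 1.96 √{(s − d²)/n}

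Example, d = 0.10, s = 0.20, n = 115: (1.072 − 0.877)/0.436 = 0.449, so power = 67%. The half-width is 1.96 √(0.19/115) = 8.0 points. The last column is the total number of patients for 80% power, from n = {(1.96√s + 0.84√(s − d²))/d}², divided by 0.144.

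| Discordance | Power, 10-point gain | Half-width, 10-point gain | Power, 5-point gain | Total patients for 80% power, 10-point gain |
|---|---|---|---|---|
| 10% | 93% | 5.5 | 39% | 529 |
| 15% | 80% | 6.8 | 28% | 802 |
| 20% | 67% | 8.0 | 22% | 1,074 |
| 30% | 50% | 9.8 | 16% | 1,619 |
| 40% | 39% | 11.4 | 13% | 2,164 |

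Simulating the paired test instead of using the formula moves the 10-point results to about 84% at 15% discordance, 70% at 20% and 40% at 40%. The 10% row is also higher than the formula shows. The picture does not change.

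**3. What searching in the cohort does.** In the main simulation (600 runs) N = 800, LVO prevalence is 14.4%, three clinical predictors carry information and three biomarkers are pure noise. Models are logistic, and the cut-off is set in the same data at 92.5% specificity.

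- One prespecified model of each kind: mean apparent gain in sensitivity 0.5 points.
- Best of six biomarker models against one clinical model: apparent gain 57.1 − 54.8, about 2.2 points before rounding. In new patients the change was 53.1 − 53.8 = −0.7 points.
- The selected model's own sensitivity was 57.1% in the cohort and 53.1% in new patients, about 3.9 points too high before rounding.

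Further runs under other assumptions, searching the biomarker side only, gave 1.9 to 4.4 points. The top figure came from a search over 36 candidates. Searching both sides equally gave 0.3 to 0.6 points.

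**The case against.** The best reply is that the hierarchy is clear elsewhere. Aim of the study, Primary study hypothesis, Endpoints and Primary endpoints all put the accuracy of the device first. The analysis section itself closes by saying that it will characterise that accuracy. On this view one badly worded sentence is the outlier, and relabelling it settles the matter. That has force, and it is why relabelling is accepted below as one of the remedies. It does not make the sentence consistent with the rest, and it leaves the conflict over models untouched.

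Four stronger readings are tempting, and the documents do not support them.

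- *The comparison is unpaired.* No section says so. Both kinds of model would be applied to the same patients, so the data are paired by design. The article is silent on the test, which a statistical analysis plan may settle.
- *Both models are certainly fitted in this cohort.* That is the plain reading of the analysis section, but two other sections describe an earlier model and preset thresholds. The document contradicts itself, and neither side can be taken as settled.
- *Useless biomarkers would nearly always appear to help.* One simulation did show an apparent gain in 95% of studies, averaging 4.4 points, but it searched 36 biomarker-eligible models against a single clinical model. The article speaks of models in the plural on both sides and does not confine the search to one.
- *A test driven by NIHSS alone would reach the targets.* The documents give no figure for this. It can only be said that the success criteria do not exclude it.

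**Conclusion.** The point holds in this form. The stated primary goal does not match the primary hypothesis, endpoint or sample size, and no effect measure or precision is attached to the difference that the goal names. The instruction to build and search models in this cohort conflicts with the use of an earlier model and preset thresholds. If followed, it makes the reported sensitivity, and any apparent biomarker gain, optimistic.

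The bias in the gain is about 0.5 points with one prespecified model of each kind or with equal searching, and about 2 to 4 points if only the biomarker side is searched. These sizes rest on illustrative simulation assumptions. Whether 800 patients suffice for the comparison cannot be told from the documents. For a 10-point gain they are about enough at 15% discordance and too few at 20% or more. For a 5-point gain they are too few throughout the range examined. Discordance is an assumption.

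**What to change.** Reconcile the analysis section with the hypothesis, the endpoint, the device description and the general Statistical analysis section:

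1. State that the primary accuracy estimate uses the LVOCheck model and threshold fixed before this study.
2. Assess added value as that fixed LVOCheck rule against one clinical-only rule with the same clinical inputs and no biomarkers, fixed from LVOCheck-Opti and BIO-FAST data at the same target specificity.
3. Report the paired difference in sensitivity among LVO patients and in specificity among non-LVO patients, each with a 95% interval.
4. Either rank this comparison explicitly, for example as first secondary, or stop calling it the primary goal. Making it co-primary is a design choice, not something that the error requires.
5. Label all models fitted or tuned in this cohort exploratory.
6. State the expected precision or detectable gain for the difference over a range of discordance.

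The cost is wording and one analysis of data that will be collected anyway. It also assumes that the earlier data allow a clinical-only rule to be fixed. The downside for the sponsor is that the added-value claim becomes harder to make and its limited power becomes visible.

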**Methods and analysis:**

This multicenter prospective observational study will include 800 patients with suspected stroke, enrolled within 24 h after symptom onset. Participants will be recruited at three Mobile Stroke Unit (MSU) sites in Berlin, Germany. Prehospital blood samples will be analyzed directly in the ambulance using the LVOCheck device. The test achieves its performance by quantifying the blood levels of the vascular biomarkers (NT-proBNP, D-Dimer, and H-FABP), and inputting these concentrations, along with neurological assessment score and patient-specific medical information such as age and blood pressure, to output predictive information on the probability of LVO stroke, together with all the input data. Additional clinical data, including final diagnoses, will be documented in electronic case report forms (eCRFs). The diagnostic performance of LVOCheck will be evaluated through comprehensive statistical analysis of the combined biomarker and clinical data, including assessment of sensitivity, specificity, and predictive models.

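### The article gives two incompatible routes to the primary accuracy estimate; under the one that searches models, the specificity target is met by construction and sensitivity is biased upward

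*Protocol article*

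**What the plan says.** All places are in the protocol article.

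- **Statistical analysis** describes a validation: "Predictions for each patient will be generated using the regression model developed in the previous phase". These predictions are compared with the confirmed diagnoses to give sensitivity, specificity, accuracy and 95% intervals.
- **Statistical analysis of the primary hypothesis** describes model development: "Multiple predictive models will be constructed to estimate each patient’s probability of LVO". The rule for choosing among them is: "Various predictive models will be examined iteratively which sensitivity is maximized while preserving a specificity level of at least 92.5" per cent. The section closes by saying that this approach characterises the real-world accuracy of the point-of-care test. It also names as its primary goal the comparison of models with and without the biomarkers.
- **Primary study hypothesis** sets the targets at 50% sensitivity and 92.5% specificity. **Primary endpoints** defines the endpoint as the accuracy of LVOCheck itself.
- **Description of the LVOCheck POCT device** says: "Respective thresholds have been determined with samples and clinical data from the first subproject", and adds the BIO-FAST study as a further source.
- **Sample size estimations** gives half-widths of 8.26 points around 75% sensitivity and 1.7 points around 95% specificity for 800 patients.

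**The concern.** A model carried over unchanged and a model chosen by iterative search in the new data are different classifiers, and they give different estimates. The article assigns both to the same primary measures and does not rank them.

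The choice matters because the search constraint is the hypothesis value. A rule that is kept only if its specificity is at least 92.5% says nothing about whether specificity reaches 92.5%. The sensitivity attached to that rule is the largest one found, so it tends to exceed what the same rule would give in new patients. It would also describe a newly selected model and not the algorithm that the App ran. The result is meant to inform triage in standard ambulances, so a few points in either measure are of practical interest.

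**Working it through.** **1. The plan's own precision figures.** Inputs from the article: N = 800 and LVO prevalence 14.4% (260/1,800). Expected counts are 800 × 0.144 = 115.2 with LVO and 800 − 115.2 = 684.8 without. Half the width of the exact (Clopper-Pearson) 95% interval is:

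- sensitivity 75%, n = 115.2: (0.8260 − 0.6607)/2 = 8.26 points;
- specificity 95%, n = 684.8: (0.9651 − 0.9309)/2 = 1.71 points.

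Both stated figures reproduce. Wald intervals would give about 7.9 and 1.63. The formula treats the classifier as fixed in advance and contains no term for model or cut-off selection.

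**2. Specificity under the search rule.** This needs no simulation. Selection requires apparent specificity ≥ 92.5% and the target is 92.5%, so the probability of appearing to meet the target is 1.

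For a locked rule applied once to 685 non-LVO patients, appearing to meet it requires at least 634/685 (92.55%). The exact binomial probabilities are:

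| True specificity | P(observed ≥ 92.5%) |
|---|---|
| 92.5% | 0.52 |
| 91% | 0.08 |
| 90% | 0.01 |

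**3. Size of the sensitivity bias.** The article gives neither the number of models nor the signal strength, so these are assumptions. The simulation used 115 LVO and 685 non-LVO patients and six normal predictors (one clinical score, three biomarkers, age, blood pressure). Models were logistic, with 400 replicates per scenario. The cut-off was set in-sample at specificity ≥ 92.5%, and true accuracy was taken from a large independent sample. The search kept the most sensitive of 35 candidate fits.

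| Signal | Procedure | Apparent sens. | True sens. | Difference (points) | True spec. |
|---|---|---|---|---|---|
| None | one model refitted | 11.5% | 8.2% | 3.3 | 91.8% |
| None | search | 19.2% | 9.6% | 9.6 | 90.4% |
| Moderate | one model refitted | 39.1% | 37.9% | 1.2 | 92.1% |
| Moderate | search | 43.6% | 37.0% | 6.6 | 91.3% |
| Good | one model refitted | 49.9% | 48.3% | 1.6 | 92.3% |
| Good | search | 54.4% | 48.2% | 6.2 | 91.3% |
| Strong | one model refitted | 71.6% | 70.1% | 1.5 | 92.2% |
| Strong | search | 74.8% | 69.6% | 5.2 | 91.6% |

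Under the search, true specificity was below 92.5% in 83% to 97% of replicates. Two further simulations with 36 candidate models gave smaller sensitivity optimism, of 4 to 5.4 points and about 3 to 4 points. True specificity was 91.5% to 91.7% in one and near 91.8% in the other. Re-picking only the cut-off of a frozen score gave almost no sensitivity bias (at most 0.2 points), but apparent specificity was still pinned at the target.

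**4. Effect on the 50% target.** In the 'good' scenario the search appeared to reach 50% sensitivity in 83% of replicates, and the selected rule truly reached it in 30%. With a frozen score and only the cut-off re-picked, the figures were 41% and 32%, so most of the gap comes from the search and the rest from sampling error.

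**The case against.** The strongest reply is that the validation route is in the article and is tied to the very measures of the primary endpoint. If it supplies the headline result, the bias does not arise. That stands, and it makes the bias conditional. It does not settle the matter, because the section headed for the primary hypothesis says something else and claims its own result as the test's accuracy.

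Second, some model building is needed for the stated comparison of biomarkers plus clinical data with clinical data alone. That also stands, and any correction must keep that comparison.

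Third, a statistical analysis plan is promised, and resampling or optimism correction would normally be specified there. Its absence here is not the complaint. The selection rule and the contradiction are written in the article, and a later plan would have to depart from one section or the other.

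Fourth, the size rests on assumed predictors and an assumed number of models. That stands; only the direction is firm.

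A reader might infer more than the text supports:

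- *That the hypothesis would go untested.* Only the specificity half is lost. Sensitivity can still fail: in the 'moderate' scenario the search appeared to reach 50% in only 10% of replicates.
- *That this is the evaluation of a finished device.* The device description says the test is still under development.
- *That an LVO-probability cut-off is known to exist.* The thresholds in the device description follow text on test-line signals and may be assay thresholds.
- *That the intervals will ignore the search.* The article says only that intervals will be computed.
- *That reuse of the same 800 patients is stated.* It is inferred, because no other data set or hold-out sample is named for these models.

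**Conclusion.** The contradiction between the two statistical sections is plain from the text and leaves the primary estimate undefined. If the search supplies it, two consequences follow. The specificity target is met by construction, which depends on no assumption. Sensitivity is biased upward, by roughly 1 to 3 points for one refitted model and roughly 3 to 10 points for a search over about 35 models, with true specificity typically about 0.5 to 2 points short of 92.5%. Those sizes depend on the assumed predictors, signal strengths and number of candidates, and on there being no hold-out sample or optimism correction, since none is named. At the upper end the bias is as large as the planned half-width of 8.26 points, which does not allow for it. The documents do not support saying that the searched model certainly is the primary analysis. The finding is that the article permits it and does not exclude it.

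**What to change.** In Statistical analysis of the primary hypothesis:

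1. State that primary sensitivity and specificity come from the previous-phase LVOCheck model with its LVO-probability cut-off, both locked before reference diagnoses are merged. If no probability cut-off exists yet, set it from LVOCheck-Opti and BIO-FAST data before that merge.
2. Remove the iterative maximisation from the primary accuracy estimate.
3. Keep the comparison of biomarker-plus-clinical with clinical-only models as a separately pre-specified analysis, and label any other refitting exploratory.
4. Report every model refitted in this cohort with bootstrap or cross-validated optimism correction that repeats model and cut-off selection in each resample.

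The cost is mainly wording, plus the work of setting a cut-off if none exists. The reported sensitivity will probably be a few points lower, and the specificity target may be missed. For a locked rule at the planning values, with 115 LVO and 685 non-LVO patients, the exact 95% lower bound exceeds 92.5% specificity with probability 0.72 (at least 648/685 needed) and exceeds 50% sensitivity with probability above 0.999 (at least 69/115 needed). Using the lower bound as the criterion is an assumption made for this illustration; the article does not set one.
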